#### Imagery exercise

During baseline assessment, all participants will be asked to identify a core nightmare, which will later be addressed in treatment. Participants are instructed to choose a nightmare that is highly emotional and part of a recurring (emotional) nightmare theme (e.g., being killed, being followed, losing someone, etc.). The core nightmare is identified for several reasons: First, given that the present treatment consists of three 60-min treatment sessions only, it seems critical to identify the most distressing nightmare(s) as early as possible in the treatment process. Second, identifying and treating one particular nightmare allows for the investigation of nightmare-specific treatment effects. For this purpose, the core nightmare will be used in a weekly imagery exercise at the beginning of each treatment session. During the exercise, participants are asked to briefly imagine their core nightmare as vividly as possible until the emotions are sufficiently reactivated (approximately 1 − 3 min). Nightmare frequency, vividness, and SUDs, as well as tolerability of negative emotions elicited by the core nightmare, and the strongest emotion experienced at the moment of nightmare reactivation are being measured after nightmare reactivation. The nightmare used in this exercise is subsequently addressed in treatment. Note that while the exercise could be mistaken for exposure, the main goal of the imagery exercise is to *reactivate* the emotions sufficiently to address them in treatment, instead of prolonged exposure to these emotions (see also section “Imagery rescripting”).

### Interventions

Both interventions (IR and IE) are written out in a detailed treatment protocol that addresses the theoretical model, treatment frame, and the use of treatment techniques. The treatments consist of three individual 60-min sessions. Within these sessions, approximately 40 min will be spent on either exposure to or rescripting of the nightmare content. The remainder of the time will be used for filling out questionnaires (± 10 min), introducing and preparing the treatment exercises (± 5 min), and a short debriefing at the conclusion of each session (± 5 min). Cognitive-behavioral therapists with a completed Master’s degree-level education in clinical psychology will deliver both interventions. The therapists were trained by the authors of the proposed study (AK, JL, NM, and AA) during two 4-h training sessions. The training involved assessment and diagnosis of nightmare disorder, and a thorough explanation of the present treatment protocol, including sample treatments and exercises. After the waiting period in the WL condition, treatment will be delivered by trained but inexperienced therapists (baccalaureate degree-level). The authors (AK and JL) will supervise all therapists weekly. Treatment sessions will be audio-recorded and independent judges blind for treatment condition will rate a random selection of audiotapes on treatment adherence.

In order to monitor treatment progress, therapists will score participants’ nightmare vividness and SUDs, as well as tolerability of negative emotions elicited by the current nightmare image, and the strongest emotion experienced at the conclusion of each IE or IR exercise. For this purpose, therapists ask participants to indicate the strength/severity of the above-named variables on a scale from 0 (“not at all”) to 10 (“very much”) after each exercise. While the number and duration of IE and IR exercises within treatment sessions can differ across individuals and sessions (approximately two to four exercises during each treatment session), the total number and duration of individual treatment sessions will be the same between all participants (i.e., three 60-min sessions; approximately 40 min spent on IE/IR). Both interventions exclude homework assignments. Also, in order to minimize possible demand effects, the explanation of the treatment rationale is kept to a minimum (see Additional file 2, for standardized treatment rationales).

#### Imagery rescripting

The IR protocol used in the proposed study is inspired by the traditional IRT treatment protocols (e.g., [12]) as well as a protocol for IR therapy for early childhood trauma [68]. In contrast to more traditional IRT techniques, the present protocol focuses exclusively on IR exercises. More specifically, treatment components such as psychoeducation about sleep, nightmares, and mental imagery, as well as keeping nightmare diaries and discussing nightmare content were discarded. Instead, participants are introduced to the rescripting technique immediately at the beginning of the first treatment session. After reactivation of the core nightmare, participants are instructed to change the nightmare in any way they wish, as long as it leads to a satisfying story. In contrast to traditional IRT and in line with trauma-focused rescripting protocols (e.g., [68]), participants are asked to actively change the nightmare *in their imagination*. Thus, instead of first thinking about how to change the nightmare and subsequently rehearsing it, nightmares are changed directly after reactivation, while the accompanying emotions are still accessible. Activation of emotional memories seems to be necessary for the adequate integration of corrective information to occur [22]. Thus, in order for rescripting to be maximally successful, it has been proposed that the negative emotions accompanying an aversive event (e.g., nightmare) should be sufficiently reactivated before rescripting [39, 69]. It is important to discriminate between a short reactivation of emotions (approximately 1–3 min) and prolonged exposure, where patients are exposed to an aversive event repeatedly and for a longer period of time (usually 45–60 min). Thus, reactivation of an aversive event within rescripting treatments is *not* considered to be exposure, but a requisite component of the rescripting technique. Within the present protocol, it is not essential to rehearse a new nightmare script as often as possible, but rather to fine-tune the new script in such a way that the negative emotions accompanying the nightmare are maximally reduced until the participant is completely satisfied with the new script and eventually feels at ease. This can be accomplished within one single rescripting exercise, but it might also take multiple exercises (possibly across multiple sessions) in order for the participant to rescript the original nightmare in such a way that they feel entirely comfortable with the new nightmare script. Note that other nightmares than the core nightmare may only be addressed in treatment if rescripting of the core nightmare is successfully achieved early in the treatment process.

#### Imaginal exposure

The IE protocol used in the proposed study is based on a standard IE intervention [70]. Contrary to other exposure-based nightmare treatments, which are based on self-help formats and might include other treatment components such as nightmare diaries and relaxation exercises (e.g., [17, 19]), the current IE treatment consist of imaginal exposure to the nightmare content only. More specifically, after shortly reactivating the core nightmare, participants are asked to vividly imagine the entire nightmare scenario in their imagination and are encouraged to focus on and experience all accompanying emotions. If necessary, possible (cognitive) avoidance tendencies are shortly discussed to subsequently eliminate them. Similar to IR, participants receive approximately 40 min IE in total during each treatment session. However, individual IE exercises can differ in length depending on the nightmare scenario, the intensity of emotions elicited by the nightmare, and/or on the level that participants are willing to fully commit to the exercise. As for IR, exposure to nightmares other than the core nightmare is only allowed if exposure to the core nightmare has caused a substantial decrease of nightmare distress early in the treatment process, and if the negative emotions accompanied by the core nightmare are completely tolerable.

### Data management and storage

All study-related data and other study material will be stored securely at the study site (UvA PsyPoli). Participant information and study data will be kept in locked cabinets in areas with limited public access. After obtaining online informed consent, participants will be allocated a unique study identifier. A password-protected file that links participants to their identifiers is stored on a secure server hosted by the UvA. Any study material concerning participant information will not be released outside of the study without written permission of the participant.

Data collected on paper during the trial will manually be entered into a database. Self-report data collected online (using an authorized UvA Qualtrics account) will be downloaded and added to the database. Data integrity will be enforced through several ways, including valid values, range checks and consistency checks. The password-protected master database will be held on a secure server hosted by the UvA, where only authorized trial personnel have access to it. All obtained data and administrative forms (e.g., informed consent) will be stored in accordance with the data storage protocol of the UvA Department of Psychology (version January 2015).

### Statistical methods

#### Outcome

Treatment effects will be analyzed on the intention-to-treat principle with mixed regression. Fixed factors in the model will include: treatment condition, time, and their interaction, as well as any relevant covariate that might reduce error. The covariance structure of the repeated part will be determined by empirically assessing the best fitting structure. If possible, random parts on the participant level will be added. For the nightmare frequency outcomes, mixed Poisson or negative binomial regression will be used. For other outcomes standard mixed regression will be used, assuming a normal distribution of residuals. If residuals show a non-normal distribution, appropriate generalized mixed models will be used (e.g., gamma regression in case of skewed distributions).

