### Sample size

The proposed study was powered to detect differences between the treatments (i.e., IR and IE) compared to the WL condition. A power calculation (two-sided, power = 80 %, alpha = 0.05; G*Power 3.1) with a medium to large effect size for individual nightmare therapy (*d* = .74; [10]) showed that 30 participants in each condition would suffice to detect a statistically significant difference between each of the two treatment conditions and the WL condition. Thus, a total of 90 participants will be included in the proposed study and potential dropouts will be replaced.

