### Sequence generation and randomization

Treatment allocation will progress in accordance with an electronically generated allocation sequence (https://www.sealedenvelope.com/simple-randomiser/v1/lists). The size of the allocation blocks (i.e., 3, 6, and 9) is randomized, and eligible participants will be stratified according to a present PTSD diagnosis to ensure that participants with PTSD are distributed equally across conditions. The allocation sequence will be stored with two independent staff members who perform the randomization, and is concealed from all researchers, therapists, and participants.

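### The efficacy model leaves baseline handling, the PTSD stratum and the test contrast unnamed; fixing them in advance would gain precision at no cost in data

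*Protocol article*

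**What the plan says.** Statistical methods, Outcome: "Fixed factors in the model will include: treatment condition, time, and their interaction, as well as any relevant covariate that might reduce error". The same section adds "For the nightmare frequency outcomes, mixed Poisson or negative binomial regression will be used"; other outcomes, including the NDIQ, get standard mixed regression with normal residuals.

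Both primary outcomes are measured at T1 to T5 (Table 1). T1 is collected at the intake interview, before randomisation. Under Procedure, the primary measures are completed at the start of each treatment session, and the first session is one week after baseline.

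On allocation, Sequence generation and randomization says "eligible participants will be stratified according to a present PTSD diagnosis". Neither statistical section mentions that stratum. Pre-treatment levels are named as covariates only in the last step of the Mediation section, not for the efficacy model.

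Sample size: "A power calculation (two-sided, power = 80 %, alpha = 0.05; G*Power 3.1" and "individual nightmare therapy (*d* = .74; [10", giving "30 participants in each condition would suffice to detect a statistically significant difference between each of the two treatment conditions and the WL condition". No baseline-post correlation is given, and the article does not say which SD the d refers to.

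**The concern.** T1 is one of the repeated assessments, so the natural reading of a condition-by-time model is that T1 is a response with its own condition effect. That effect allows for a true difference between arms at T1, which randomisation rules out. Estimating it costs precision.

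The open covariate clause and the unnamed contrast leave choices that affect the result. Nothing in the article says when the relevant covariates are fixed or which interaction term decides whether a treatment beats WL. The PTSD diagnosis was important enough to balance by design, yet its place in the model is left to the same clause.

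At stake are precision in a trial that the Discussion itself calls relatively small, and protection against a model chosen with outcome data in view.

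**Working it through.** **Inputs from the protocol article.** Two-sided alpha 0.05, d = 0.74, 30 per arm, each treatment against WL.

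**Assumed inputs.** Baseline-post correlation r, shown over a range. Equal SDs at T1 and T5. d standardised on the post-score SD. A linear model, so the results apply to the NDIQ.

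**Step 1: reproduce the planned size.** A two-sample t test (noncentral t, df = 2n − 2) at d = 0.74 gives power 79.1% at n = 29 and 80.5% at n = 30. The stated 30 per arm is therefore a comparison of single scores that makes no use of baseline.

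**Step 2: variance of the two contrasts**, in units of the post-score variance.
- T5 minus T1 with a free T1 effect: 2(1 − r).
- Baseline-adjusted: 1 − r².
- Ratio, adjusted to change: (1 − r²) / [2(1 − r)] = (1 + r)/2.

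**Step 3: power at 30 per arm.** Effective d is 0.74 divided by the square root of the variance factor (df 58 for change, 57 adjusted).

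| assumed r | 2(1 − r) | 1 − r² | ratio | power, change | power, adjusted |
|---|---|---|---|---|---|
| 0.3 | 1.40 | 0.91 | 0.65 | 66.4% | 84.0% |
| 0.4 | 1.20 | 0.84 | 0.70 | 73.0% | 86.7% |
| 0.5 | 1.00 | 0.75 | 0.75 | 80.5% | 90.2% |
| 0.7 | 0.60 | 0.51 | 0.85 | 95.3% | 97.6% |

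Example at r = 0.3: 0.74/√1.40 = 0.625 for change and 0.74/√0.91 = 0.776 adjusted. The change contrast reaches 80% power at r of about 0.49. At r = 0.3 it would need 42 per arm, against 28 with adjustment.

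**Step 4: does another contrast rescue the power?** Take the mean of T2 to T5 minus T1, with compound symmetry. Its variance is (1 + 3r)/4 + 1 − 2r, which is 0.875 at r = 0.3. If the full effect were present at all four assessments, power would be 85.4%. But T2 is completed at the start of the first session, before any treatment. With no effect at T2 and the full effect at T3 to T5, the mean effect is 0.74 × 3/4 = 0.555, and 0.555/√0.875 = 0.593 gives 62% power. The choice of contrast therefore matters.

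**Step 5: the PTSD stratum.** A PTSD effect that shifts T1 and T5 equally cancels in T5 minus T1. In a simulation (30 per arm, stratum balanced, PTSD explaining an assumed 10% of variance, r = 0.3, 20,000 runs), the change contrast had type I error of about 5% and power of about 66%, with or without the stratum term.

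**The case against.** The strongest reply is that the plan excludes nothing. The covariate clause can admit both the T1 score and the PTSD stratum, T1 is already used as a repeated assessment, and an article may leave the exact covariate list to an analysis plan that is not shown. This stands to the extent that the terms are unnamed, not ruled out. It does not remove the point, because the article does state the fixed factors of its efficacy model, and a more precise form is available from data already collected.

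A reader might infer more than the documents support, in four ways:

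- **That the trial is underpowered.** This needs r below about 0.49, d on the post-score SD and a T5-minus-T1 contrast. The article gives none of these. If d is on the change-score SD, there is no shortfall.
- **That the shortfall applies to both primary outcomes.** The number of nightmares is to be analysed by Poisson or negative binomial regression, where these variance factors do not apply directly.
- **That omitting the stratum distorts the error rate or costs appreciable power.** That could arise for a comparison of T5 scores alone. It does not follow for the change contrast, where a stable PTSD effect cancels.
- **That therapist clustering makes the tests anti-conservative.** The Interventions section says "Cognitive-behavioral therapists with a completed Master’s degree-level education in clinical psychology will deliver both interventions", and WL has no therapist during the analysed period, so clustering is possible in the active arms. The number of therapists, their caseloads and the intraclass correlation are not given, so no size can be put on it.

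**Conclusion.** The point holds as one of precision and advance specification, not of validity. The condition-by-time analysis with T1 as a response is unbiased. It gives away 35%, 25% or 15% of the variance at assumed r of 0.3, 0.5 or 0.7, compared with a baseline-adjusted version of the same model. In power terms, for the NDIQ with d on the post-score SD, that is 66% v 84%, 80% v 90% and 95% v 98%. The proportional gain from adjustment does not depend on how d was standardised; the shortfall against 80% does.

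The case for naming the PTSD stratum is that it belongs to the design and should not be an optional covariate. It does not rest on a calculated gain. The primary contrast also needs naming, because averaging over assessments would include T2, which precedes treatment.

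**What to change.** State before analysis, in the statistical methods or the analysis plan:

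- The primary model constrains T1 means to be equal across arms, or uses T1 as a covariate. For the nightmare count, log(T1 count + 1) can serve as the covariate.
- PTSD stratum is a fixed term.
- The primary tests are IR v WL and IE v WL at T5.
- No covariate of the primary model is chosen after outcome data have been seen.

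It would also help to say which SD the d of 0.74 refers to. A therapist random effect in the active arms could be listed as an optional sensitivity analysis, accepting that its variance may be poorly estimated if there are few therapists.

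The cost is wording only: T1 scores and PTSD diagnosis are already collected, and the sample size does not change.

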#### Primary outcome measures

The first primary outcome measure addresses *nightmare frequency.* There are two ways to measure nightmare frequency with the widely used Nightmare Frequency Questionnaire (NFQ; [56]). This instrument assesses (1) the number of nights with nightmares in the last week, and (2) the total number of nightmares in the last week. As most previous nightmare research is focused on the latter, rather than the former conceptualization of nightmare frequency (e.g., [11, 13]), the total number of nightmares in the last week constitutes the first primary outcome measure, while the number of nights with nightmares in the last week is considered a secondary outcome measure. Both variables are assessed by means of a one-question, self-report survey (see NFQ; [56]).

The second primary outcome measure addresses *distress caused by nightmares* and the impact of nightmares on everyday life as well as on sleep behavior, which is assessed with a 12-item measurement instrument constructed for this study. For this purpose, several items of the Nightmare Distress Questionnaire (NDQ; [57]) and the Nightmare Effect Survey (NES; [58]) were modified and served as a basis for the new survey. This newly developed Nightmare Distress and Impact Questionnaire (NDIQ) consists of two subscales. The first subscale addresses the impact caused by nightmares during the day (e.g., “Because of my nightmares, I cannot function properly during the day”), while the second subscale is focused on the distress caused by nightmares at night (e.g., “My nightmares disturb my sleep pattern”). Given that nightmares do not only cause sleep complaints, but also severe daytime suffering, the authors aimed at constructing a questionnaire that could clearly distinguish these two sources of nightmare distress. Items of the NDIQ are scored on a four-point scale: 0 (Not), 1 (A little bit), 2 (Somewhat), and 3 (Completely). Validation of this questionnaire is still ongoing. The sumscore of both subscales constitutes the second primary outcome measure, while possible effects of IR and IE on the two subscales will be explored separately.

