#### Secondary outcome measures

The Zelf Inventarisatie Lijst (ZIL; [59]) will be used to measure *symptoms of posttraumatic stress disorder*. The ZIL is a 22-item Dutch self-report inventory covering the severity of PTSD symptoms in the last 4 weeks. In contrast to other measures of PTSD symptoms, the ZIL allows for the assessment of posttraumatic symptoms irrespective of the occurrence of a traumatic event. Given that the proposed study aims to include participants with posttraumatic as well as idiopathic nightmares, it is assumed that (at least) some participants will not have experienced a traumatic event. The ZIL, therefore, seems to be a suitable measure of PTSD symptom severity in the present sample. The reliability of the scale is good, with Cronbach’s *α* varying from 0.90 to 0.94 [60], and a test-retest reliability of 0.92 [61].

*Sleep complaints* will be assessed with the Dutch version of the Insomnia Severity Index (ISI; [62]). The English questionnaire is a valid and reliable measure to detect changes in insomnia severity (internal consistency = 0.78; [63]). Validation studies on the Dutch version of this questionnaire are not yet published.

*Dysfunctional beliefs* about nightmares will be measured with a newly developed Nightmare Beliefs Questionnaire (NBQ). The NBQ was constructed based on nightmare interviews with four pilot participants of the proposed study. Given that dysfunctional beliefs have been shown to play an important role in sleep disorders (e.g., [64]) as well as other psychological disorders (e.g., [36, 65, 66]), it seems worthwhile to construct a measure that can assesses such dysfunctional beliefs about nightmares. The NBQ is a 15-item self-report questionnaire that measures the degree to which patients hold certain beliefs about nightmares (e.g., “People who suffer from nightmares are weak” or “I cannot control my nightmares”). Items of the NBQ are scored on a four-point scale: 0 (Not), 1 (A little bit), 2 (Somewhat), and 3 (Completely). Outcome values consist of the sum of all items, which can range from 0 to 45. The principal investigators (AK and JL) created the NBQ for the purpose of the proposed trial. Validation of this questionnaire is still ongoing.

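### Nights with nightmares cannot exceed seven, so the assigned Poisson or negative binomial model usually overstates its standard errors; gamma is also a poor fallback example for scores that can be zero

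*Protocol article*

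**What the plan says.** The protocol article, under Primary outcome measures, describes two ways of measuring nightmare frequency: "1) the number of nights with nightmares in the last week, and (2) the total number of nightmares in the last week". The total is the first primary outcome; "the number of nights with nightmares in the last week is considered a secondary outcome measure". Table 1 lists both, at every assessment from T1 to F2.

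Under Statistical methods, Outcome, both measures receive the same model without qualification: "For the nightmare frequency outcomes, mixed Poisson or negative binomial regression will be used". The fixed effects are condition, time and their interaction. Participant-level random parts are added if possible.

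The rest follow a separate rule: "For other outcomes standard mixed regression will be used, assuming a normal distribution of residuals". A conditional fallback comes after it: "If residuals show a non-normal distribution, appropriate generalized mixed models will be used (e.g., gamma regression in case of skewed distributions". Two of the scales under this rule have a documented zero. For the second primary outcome, "Items of the NDIQ are scored on a four-point scale: 0 (Not), 1 (A little bit), 2 (Somewhat), and 3 (Completely", with 12 items. For the NBQ, "Outcome values consist of the sum of all items, which can range from 0 to 45".

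**The concern.** A week has seven nights, so nights with a nightmare is a bounded measure. Poisson regression sets the variance equal to the mean, and negative binomial sets it above. A proportion out of seven usually varies less than that within a person. Choosing between the two named families cannot repair this, because both err in the same direction. What is at stake is precision: intervals that are too wide and a conservative test for a secondary outcome, in a trial whose Discussion already calls its sample relatively small. Both families also place probability on impossible values above 7.

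The gamma example raises a lesser worry. Skewed residuals on a symptom score after effective treatment would plausibly come with scores at or near zero, which is where gamma fails.

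**Working it through.** **Inputs.** From the article: two frequency measures, one capped at 7; the named families; NDIQ 12 items scored 0-3; NBQ range 0-45; 30 participants per condition. The article gives no mean number of nights and no correlation, so means of 2, 3.5 and 5 nights and a range of correlations are assumed.

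**The plan's own figure.** The article gives none on this point. Its sample size reproduces: a two-sample t-test with d = 0.74 and two-sided alpha 0.05 has power 79.1% at 29 per arm and 80.5% at 30. That calculation does not depend on the model family and is unaffected.

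**Step 1: pure binomial variation.** With mean m and p = m/7, the binomial variance is m(1 - m/7) and the Poisson variance is m. The ratio of the Poisson to the binomial standard error is 1/√(1 - m/7).

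| Mean nights | Poisson variance | Binomial variance | SE ratio | Poisson P(Y > 7) |
|---|---|---|---|---|
| 2 | 2.00 | 1.43 | 1.18 | 0.1% |
| 3.5 | 3.50 | 1.75 | 1.41 | 2.7% |
| 5 | 5.00 | 1.43 | 1.87 | 13.3% |

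Negative binomial variance is m + m²/k, which is further from the target.

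**Step 2: stable differences between people, absorbed by a random intercept.** With intraclass correlation ρ, the average within-person variance is 7p(1 - p)(1 - ρ), so the ratio becomes 1/√[(1 - m/7)(1 - ρ)]. For ρ from 0.1 to 0.4:

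- mean 2: 1/√(0.714 × 0.9) = 1.25 to 1/√(0.714 × 0.6) = 1.53
- mean 3.5: 1/√(0.5 × 0.9) = 1.49 to 1/√(0.5 × 0.6) = 1.83
- mean 5: 1/√(0.286 × 0.9) = 1.97 to 1/√(0.286 × 0.6) = 2.42

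A simulation agrees. It used a random-intercept Poisson model, two time points, 30 per arm, no true effect, and each person's probability constant over time. Model SE of the condition-by-time term divided by its true SD was 1.25-1.60, 1.44-1.89 and 1.90-2.38 at the three means. Rejection at nominal 5% was 0-1.3%.

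**Step 3: week-to-week variation in a person's probability.** If this induces correlation r between nights of the same week, the within-person variance is 7p(1 - p)(1 + 6r). It passes the mean when r exceeds [1/(1 - m/7) - 1]/6:

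- mean 2: (1.4 - 1)/6 = 0.07
- mean 3.5: (2 - 1)/6 = 0.17
- mean 5: (3.5 - 1)/6 = 0.42

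A second simulation of the same layout gave ratios of about 1.2 to 2.05 with constant probabilities and about 1.0 to 1.7 with extra week-to-week variation.

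**Step 4: no random effects.** For one time point at mean 3.5, plain Poisson had type I error 0.8%, 2.5%, 6.7% and 12.8% at intraclass correlations 0, 0.1, 0.2 and 0.4. With an estimated dispersion it was 4.6-4.9%.

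**Step 5: gamma at zero.** NDIQ ranges 0 to 12 × 3 = 36 and NBQ 0 to 15 × 3 = 45. The gamma log-density at 0 is minus infinity for shape above 1, plus infinity for shape below 1, and finite only at shape 1. A trial gamma fit with one zero among 60 values returned an infinite log-likelihood, although its mean coefficients were finite.

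**The case against.** The best reply on nights is that a cap at 7 does not by itself put the variance below the mean. A 0-7 variable with mean m can have variance up to m(7 - m), which exceeds m for any mean below 6. Step 3 shows how little week-to-week correlation is needed at low means, and Step 4 shows that the error can reverse if between-person spread is not absorbed. An estimated scale parameter would also largely cure the standard errors. All of this stands, and it is why the point is worded as usually, with assumed means. It does not remove the point: participant random effects are planned where possible, the Outcome section does not mention an estimated dispersion for the count models, and a binomial-type model respects the bound in every case.

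On gamma, the reply is stronger. The default for NDIQ and NBQ is a normal mixed model, and gamma is only an example within a clause that already asks for an appropriate model.

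A reader might infer more than the article supports:

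- That the named distributions misfit in general. They do not: the count families suit total nightmares, the first primary outcome.
- That zero scores would be deleted and good responders lost from a primary outcome. The article says nothing of deleting or shifting scores, specifies intention-to-treat, and gives no zero rate.
- That the ISI shares the problem. Its range is not given; nor is a zero on the ZIL shown.
- That the fallback turns a mean difference into a ratio. That needs a log link, and none is named.

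**Conclusion.** The point holds for the nights outcome, as a misspecification of one secondary measure. Under pure binomial variation the standard errors are too large by a factor of 1.18 to 1.87 over means of 2 to 5 nights. Stable between-person differences absorbed by random effects increase the factor; week-to-week variation reduces it, to about none at 2 nights. The usual consequence is lost power rather than false positives. These sizes rest on assumed means and correlations and on a simplified two-time-point layout, not on trial data.

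The gamma remark is minor. It is a poor choice of example for scores that can be zero, not a commitment to an unworkable analysis. The sample size, the model for total nightmares and the default model for NDIQ are not called into question.

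**What to change.** Separate the two frequency outcomes in the Outcome section. Analyse nights with a nightmare by binomial or beta-binomial mixed regression with denominator 7; the beta-binomial also allows for week-to-week variation. Keep Poisson or negative binomial for the total number of nightmares.

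In the fallback sentence, replace gamma with a family that admits zeros and the upper bound, such as beta-binomial or ordinal. Alternatively, keep the linear mixed model with bootstrap or robust standard errors when residuals are skewed. Either is defensible; robust errors with 30 per arm have small-sample costs of their own.

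The cost is two sentences of wording, one different model to fit, and an odds ratio instead of a rate ratio for nights. No new data are needed.
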